### Participant timeline {13}

The time schedule is provided via the schematic diagram below (Fig. 3). The entire experiment will last for approximately 1–1.5 h for each participant.

**Fig. 3 Fig3:**
[figure not shown]
Schedule of enrollment, interventions, and assessments of the study

### Sample size {14}

To estimate the required sample size, we conducted a simulation analysis on the intervention effect on writing performance using ordinary least squares (OLS) regression. Recent empirical evidence suggests that the effect size of generative AI on writing tasks ranges around Cohen’s *d* = 0.4–0.5, such as [1, 48]. In our simulation analysis, the simulated data assumes normally distributed data, equal and standardized standard deviations between the two conditions, and an anticipated effect size of Cohen’s *d* = 0.45. In the end, our analysis indicated that recruiting a minimum of 160 participants would be necessary to achieve a statistical power greater than 0.8 under an alpha level of 0.05. The simulation was implemented in R, and the corresponding code is available at the Open Science Framework (OSF) via https://osf.io/9jgme/.

We opt to base our sample size estimation on writing performance, but not on the other primary outcome, cognitive effort, for two reasons. First, the effect of generative AI on performance outcomes has been studied [1, 48], but we did not find prior evidence on the effect size of generative AI on cognitive effort using physiological measures. Second, our physiological measure of cognitive effort may likely be powered once the sample size satisfies our behavioral measure of writing performance. Pupillometry studies on cognitive efforts, such as the N-back test, typically recruit 20–50 participants in short, repeated, within-subject trials (e.g., [49]). These studies provide a general estimation of participants needed. Although our study design (i.e., a between-subject RCT) differs from common pupillometry studies, cognitive effort is still a repeated outcome measure using time series pupil data throughout the entire writing process. Repeated outcome measures generally can enhance statistical power by taking into account within-subject variability [50].

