**Methods:**

This study is a randomized controlled lab experiment that compares the effects of using generative AI (intervention group) versus not using it (control group) on cognitive effort and writing performance in an analytical writing task designed as a hypothetical writing class assignment for college students. During the experiment, eye-tracking technology will monitor eye movements and pupil dilation. Functional near-infrared spectroscopy (fNIRS) will collect brain hemodynamic responses. A survey will measure individuals’ perceptions of the writing task and their attitudes on generative AI. We will recruit 160 participants (aged 18–35 years) from a German university where the research will be conducted.

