### Recruitment {15}

The recruitment will follow a convenience sampling strategy. To aim for a student population with diverse academic backgrounds, participants will be recruited broadly through social media platforms, email lists, and flyers at the research university where the experiment will be conducted. Given that the experiment will start during the summer, the research team can recruit summer school students as participants. Thus, the study sample will not be limited to the students presently at the university. The recruitment materials include a brief description of the study, the eligibility criteria for participation, and the compensation for participation. Individuals who are interested in participation can sign up on a calendar by selecting available time slots provided by the experimenters. Participants will receive 30 euros in compensation upon completion of the experiment. Participants who withdraw in the middle of the experiment will receive partial compensation, prorated based on the amount of time they spend in the experiment.

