## Statistical methods

### Statistical methods for primary and secondary outcomes {20a}

Here, the intervention effect on the two primary outcomes will be estimated by an intent-to-treat analysis. Our first primary outcome, writing performance, will be treated as a continuous variable. Our second primary outcome, cognitive effort as measured by mean changes in pupil size, will also be treated as a continuous variable. We will estimate the intervention effect on each outcome separately using ordinary least squares (OLS) regression with heteroskedasticity-robust standard errors. To control for type I error inflation due to multiple testing, we will apply a Bonferroni correction. Accordingly, the adjusted significance threshold is set at *α* = 0.05/2 = 0.025. The outcome of cognitive effort is a psychophysiological measure recorded throughout the entire writing process. Standard pre-processing steps will be taken before the statistical analysis [51, 52], such as correcting for screen angle distortion, removing invalid data that do not reflect the actual pupil size (pupil size below 1.5 mm or over 9 mm [53], often due to blinking), smoothing to remove small oscillatory and noise activity, interpolating blink related invalid data, downsampling, and correcting pupil size changes based on the baseline pupil size that will be collected during a 30-s relaxation task at the beginning of the experiment. Participant-level data will be excluded if the data do not meet basic quality standards, such as having a high proportion of invalid data.

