### Methods in analysis to handle protocol non-adherence and any statistical methods to handle missing data {20c}

During the lab experiment, we will monitor and control for missingness in the survey data due to non-adherence under 20%. If the missingness is less than 5%, we will conduct a complete case analysis, which removes participants with missing responses [57, 58]. If the missingness falls between 5 and 20%, we will apply multiple imputation using the rest of the survey data [59].

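### The 160 participants to be recruited are the number that must be analysed for 80% power, so the stated power has almost no room for the losses the plan permits

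*Protocol article*

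**What the plan says.** Under Sample size {14}, the protocol reports a simulation for writing performance analysed by OLS. The inputs are "an anticipated effect size of Cohen’s *d* = 0.45" and a data model in which "the simulated data assumes normally distributed data, equal and standardized standard deviations between the two conditions". The result is that "recruiting a minimum of 160 participants would be necessary to achieve a statistical power greater than 0.8 under an alpha level of 0.05". No term for loss is listed. The abstract sets enrolment at the same figure: "We will recruit 160 participants (aged 18–35 years) from a German university where the research will be conducted".

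The same section gives no calculation for the other primary outcome, pupil-based cognitive effort. It suggests that this outcome is probably adequately powered once the writing outcome is.

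Elsewhere the plan provides for participants or records to be lost:

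- Recruitment {15}: "Participants who withdraw in the middle of the experiment will receive partial compensation, prorated based on the amount of time they spend in the experiment". Sections {11b}, {18b} and {26a} also say that withdrawal is possible at any time.
- Confidentiality {27}: contact details are kept partly so that a participant can have their data withdrawn.
- Statistical methods {20a}, in the text on pupil pre-processing: "Participant-level data will be excluded if the data do not meet basic quality standards, such as having a high proportion of invalid data".
- Section {17b}: participants whose condition is accidentally revealed are excluded, but are not counted in the randomised sequence.
- Section {20c}: "we will monitor and control for missingness in the survey data due to non-adherence under 20"%, with complete-case analysis below 5% and multiple imputation from 5 to 20%.

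**The concern.** A sample size calculation gives the number of participants whose outcome must enter the analysis. If that number is also the number enrolled, the stated power holds only when almost nobody is lost. This plan permits loss by several routes and does not say that those lost will be made up, except that accidental-reveal cases fall outside the sequence count.

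At stake is how a null result on writing performance will be read: against a power above 0.8 that the enrolment may not deliver. The pupil outcome is more exposed. It has no power figure of its own, and it is the outcome to which the quality exclusion is written. The section leans on repeated measurement, but section {20a} analyses mean pupil change per participant by OLS, so an excluded participant contributes nothing.

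**Working it through.** **Inputs.** d = 0.45, SD 1 in both arms, normal data, alpha 0.05 (Sample size {14}); 1:1 allocation (Trial design {8}); OLS on treatment alone, which is equivalent to a two-sample t-test. Sidedness is not stated. I take it as two-sided, because a one-sided test at 0.05 would need only 124.

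**Reproducing the plan's figure.** The normal approximation per arm is n = 2(z₀.₉₇₅ + z₀.₈)² / d² = 2(1.960 + 0.842)² / 0.45² ≈ 77.5. That rounds up to 78 per arm, 156 in total. The exact noncentral t calculation gives 78.49, so 79 per arm and 158 in total. The plan's 160 agrees with this. It is the complete-data number with no inflation: had attrition been built in, 160 would lie clearly above 158.

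**Power at smaller analysed numbers.** With n per arm = N/2, the noncentrality is δ = d·√(n/2) on 2n − 2 degrees of freedom. At N = 160, δ = 0.45·√40 = 2.846. The normal approximation gives Φ(2.846 − 1.960) = 0.812, the t calculation gives 0.808, and a simulation of 200,000 runs also gives 0.808. The table uses the t calculation and assumes equal arms.

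| Analysed N | Lost of 160 | Power, alpha 0.05 | Power, alpha 0.025 |
|---|---|---|---|
| 160 | 0 | 0.808 | 0.720 |
| 158 | 2 | 0.803 | 0.714 |
| 156 | 4 (2.5%) | 0.797 | 0.707 |
| 152 | 8 (5%) | 0.787 | 0.695 |
| 144 | 16 (10%) | 0.765 | 0.668 |

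The last column is there because section {20a} tests each primary outcome at 0.05/2 = 0.025, while the sample size section uses 0.05. That mismatch is a separate defect and the larger one: 0.720 with nobody lost. The loss point does not depend on it, since it already holds at the plan's own 0.05.

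**Which losses touch the powered outcome.** The powered outcome is the essay score, and its first analysis is unadjusted. Withdrawal before an essay is submitted and withdrawal of data both reduce it. Pupil quality exclusions do not. Missing survey items do not remove anyone from an unadjusted analysis of the essay score.

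**The case against.** The strongest reply is that the shortfall on writing performance is small. Each participant attends one session of about 1 to 1.5 hours, there is no follow-up, and full payment comes on completion, so few essays should be lost. An assumed 5% loss costs about two points (0.808 to 0.787). The plan's own range of effect sizes, d = 0.4 to 0.5, moves power at N = 160 far more, from 0.71 to 0.88. This stands, and it limits the point to a modest one.

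Two offsets can also be raised. The sample size section calls 160 a minimum, which allows over-recruitment, but the abstract gives 160 as the number to recruit. The planned covariate adjustment may recover some power: if covariates explained 5% of the variance, power at N = 152 would be 0.807, and if 10%, the same at N = 144. Those R² values are assumptions, the protocol gives none, and the unadjusted analysis comes first.

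A reader might go further, take the 20% in section {20c} as a tolerated loss of the primary outcome, and read power off at N = 128 (0.71). The document does not support that. The ceiling concerns survey data, missingness of 5 to 20% is to be imputed rather than dropped, and section {18a} lists the final essay separately from the survey responses. Likewise, pupil exclusions cannot be said to lower a stated power, since none was calculated for that outcome.

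Nor is this a detail left to a fuller document. Section {31c} calls the article the full protocol, and the recruitment number and its power are both stated there.

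**Conclusion.** The plan's arithmetic is correct for 160 analysed. What does not hold is the use of that figure as a recruitment number with no allowance for loss. The margin is about two participants, and power for writing performance falls below 0.80 once about four are lost. Over an assumed essay loss of 2.5 to 10%, power is 0.80 to 0.76 at alpha 0.05, and about 0.71 to 0.67 at the 0.025 actually tested. This rests on d = 0.45, a two-sided test, equal arms and no gain from covariates. The loss range is my assumption, because the document gives no rate.

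For the pupil outcome the conclusion is qualitative: its power is uncalculated, and it will be analysed on fewer participants to whatever extent records fail the quality check. The text should be changed, but the effect on writing performance is modest.

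**What to change.** In Sample size {14}:

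1. State that 160 is the number analysed without loss.
2. Restate power for writing performance over a small assumed loss range, at the alpha actually tested. At 0.025 this is 0.72 with 160 analysed, 0.69 with 152 and 0.67 with 144. Label the loss rates as assumptions.
3. Say that no power was calculated for the pupil outcome and that quality exclusions will reduce its analysed number, and qualify the suggestion that it is probably powered at the same N.

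No rule for replacing withdrawn participants is needed. One would make the target depend on completion, which sits awkwardly with the intention-to-treat analysis when the arms are not blinded to the intervention.

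The cost is a few lines and a rerun of the existing R simulation at lower N and at 0.025. The downside is that the stated power becomes less favourable.

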### Outcomes {12}

The study has two primary outcomes. First, we will measure participants’ writing performance scores on the analytical writing task. The task is adapted from the Analytical Writing section in the GRE, a worldwide standardized computer-based exam developed by the Educational Testing Service (ETS) [27]. Participants’ writing performance will be scored using the GRE 0–6 rubric and by an automatic essay-scoring platform called *ScoreItNow!*, which is powered by ETS’s e-rater engine [32, 33]. We chose to adapt from the GRE writing materials for two reasons. First, their writing task and grading rubrics were established writing materials designed to measure critical thinking and analytical writing skills and have been used in research as practice materials for writing (e.g. [34]). Second, OpenAI’s technical report shows that ChatGPT (GPT-4) can score 4 out of 6 (~ 54th percentile) on the GRE analytical writing task [31]. This gives us a benchmark for assessing the potential increase in writing performance when individuals collaborate with generative AI.

Second, we will measure participants’ cognitive effort during the writing process. Participants’ cognitive effort will be measured using a psychophysiological proxy—i.e., changes in pupil size [35, 36]. Pupil diameter and gaze data will be collected using the Tobii Pro Fusion eye tracker at a sampling rate of 120 Hz. During the preparation stage of the study, the room light will be adjusted so that the illuminance at the participants’ eyes is at a constant value of 320 LUX. Baseline pupil diameters will be recorded during a resting task in the experiment preparation stage that asks the participant to stare at a cross that will appear for 10 s each on the left, center, and right sections of the computer screen. Pupil diameters and gaze data will be recorded throughout the writing process.

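### The sample size is justified at alpha 0.05, but each primary outcome is tested at 0.025, where power for writing performance at d = 0.45 is about 0.72, not above 0.8

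*Protocol article*

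**What the plan says.** The Outcomes section {12} of the protocol article declares two primary outcomes, writing performance and cognitive effort measured by pupil size: "The study has two primary outcomes".

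The Sample size section {14} rests on writing performance alone. It takes "an anticipated effect size of Cohen’s *d* = 0.45" from a cited range of 0.4 to 0.5. For the data it says that "the simulated data assumes normally distributed data, equal and standardized standard deviations between the two conditions". It concludes that "recruiting a minimum of 160 participants would be necessary to achieve a statistical power greater than 0.8 under an alpha level of 0.05".

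The Statistical methods section {20a} analyses the two primary outcomes separately by OLS with robust standard errors. On multiplicity it says: "To control for type I error inflation due to multiple testing, we will apply a Bonferroni correction". The consequence is stated outright: "the adjusted significance threshold is set at *α* = 0.05/2 = 0.025".

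The Sample size section does not mention 0.025, and no other section adds participants to allow for it.

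**The concern.** The alpha used to size the trial is twice the alpha used to judge the outcome on which it was sized. Power falls when the threshold is tightened, so a sample chosen to pass 0.8 only narrowly at 0.05 cannot be expected to pass it at 0.025.

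The stake is how a null result is read. If the writing comparison misses 0.025, readers will set it against a trial said to have more than 80% power. At the planned effect the type II error is about 28% (1 − 0.72), not below 20%. The plan also leans on this calculation for the pupil outcome, which it expects to be adequately powered once the sample suffices for writing performance.

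**Working it through.** **Inputs**
- Effect d = 0.45, cited range 0.4 to 0.5, SD 1 in both arms, normal data (Sample size {14}).
- N = 160 (Sample size {14}), allocated 1:1 (Trial design {8}), so n = 80 per arm.
- Alpha for sizing 0.05 (Sample size {14}); alpha for testing 0.05/2 = 0.025 (Statistical methods {20a}).
- Assumption: two-sided tests. The protocol does not state sidedness; the check in step 1 supports this reading.

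**Formula.** For a two-sample comparison of means with n per arm, the noncentrality is d × √(n/2) on 2n − 2 degrees of freedom. Here it is 0.45 × √40 = 2.846 on 158 df. Power is the probability that a noncentral t with these parameters exceeds the two-sided critical value in absolute size. The normal approximation is Φ(2.846 − z), with z the critical value for 1 − alpha/2.

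**Step 1: reproduce the plan's figure (alpha 0.05).**
- Normal approximation: Φ(2.846 − 1.960) = Φ(0.886) = 0.812.
- Exact t: 0.808.
- One-sided 0.05 would give about 0.88.

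The plan's claim of power just above 0.8 with 160 participants is therefore reproduced, and it fits a two-sided test at 0.05.

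**Step 2: the same design at the threshold that will be used (alpha 0.025).**
- Normal approximation: Φ(2.846 − 2.241) = Φ(0.605) = 0.727.
- Exact t: 0.720.
- Simulation of 200,000 trials with robust standard errors: 0.714 to 0.719, depending on the robust variant.

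**Step 3: over the plan's own effect range** (80 per arm, exact t).

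| d | Power at 0.05 | Power at 0.025 |
|---|---|---|
| 0.40 | 0.71 | 0.61 |
| 0.45 | 0.81 | 0.72 |
| 0.50 | 0.88 | 0.81 |

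**Step 4: what 160 participants can detect at 0.025, and what 0.45 would need.**
- Detectable effect at 80% power, normal approximation: (2.241 + 0.842) × √(2/80) = 3.083 × 0.158 = 0.487. The exact t gives 0.491. Both round to 0.49.
- Sample size for 80% power at d = 0.45: 96 per arm, 192 in all (exact t), or 188 in all (normal approximation).

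**Step 5: what Holm would recover.** Under Holm, writing performance is tested at 0.05 whenever the pupil outcome is significant at 0.025. If the two outcomes are assumed independent, power for writing is 0.720 + (0.808 − 0.720) × P, where P is the power of the pupil test at 0.025. The plan gives no pupil effect size, so P has to be assumed:
- P = 0.3: 0.746
- P = 0.5: 0.764
- P = 0.72: 0.783

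All three remain below 0.8.

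**The case against.** **The statement is true as worded.** The Sample size section says power exceeds 0.8 at alpha 0.05, and that reproduces. This stands: there is no slip in the arithmetic. The fault is that the alpha quoted is not the alpha of the planned test.

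**The 0.025 might be one-sided.** If so, power would stay at about 0.81. But the protocol obtains 0.025 by dividing 0.05 by two for two outcomes, not by halving for direction, and the sample size fits a two-sided 0.05.

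**Covariate adjustment may recover the loss.** The plan does add a model with four self-reported variables, partly for power. As an assumption, covariates explaining 10%, 17% or 20% of the variance would give power of about 0.77, 0.80 or 0.82 at 0.025. The plan states no such figure, runs the unadjusted model first and takes no credit for adjustment in the sample size. So this does not close the gap, but it does mean that 0.72 is not a ceiling. Nor is it one at the top of the cited effect range, where power is 0.81.

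**The study is described as exploratory, and no bias follows.** Both are correct, and both limit the seriousness. They do not make the two alphas agree.

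**A reader might infer that exclusions lower the writing power further.** The documents do not support that. The data-quality exclusion closes the account of pupil pre-processing and gives no ground for discarding an essay score. Participants excluded because their condition was revealed are not counted in the randomized sequence (Procedure for unblinding {17b}), which suggests that they are replaced. No loss rate is given for an essay written in a single session.

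**Conclusion.** The concern holds as an inconsistency between two sections that leaves the stated power wrong for the planned primary test. For writing performance, power at the 0.025 threshold is about 0.72 at d = 0.45, some 9 percentage points below the 0.81 that the same design has at 0.05. It exceeds 0.8 only for effects of about 0.49 or more, near the top of the plan's cited range.

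This rests on a two-sided, unadjusted comparison with 80 per arm, normal data and equal SDs, as in the plan's own simulation. It applies to writing performance only, because the protocol gives no effect size for the pupil measure. A reader might go further and conclude that the trial is invalid or must be enlarged. Neither follows: Bonferroni is a valid correction, and the sample can stay at 160 provided its power is described correctly.

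**What to change.** 1. Rerun the posted simulation with alpha 0.025 and correct the Sample size section. It should say that 160 participants give power of about 0.72 for d = 0.45 (0.61 at 0.40, 0.81 at 0.50), or equivalently 80% power for d of about 0.49, at the Bonferroni threshold. State that the test is two-sided, and no longer present 160 as the minimum for power above 0.8.

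2. Optionally, replace Bonferroni by Holm for the two primary outcomes: test the smaller p-value at 0.025 and, if it is significant, the other at 0.05. Holm keeps the family-wise error at 0.05 and is never less powerful. Under the assumptions in the working (independent outcomes, pupil power of 0.3 to 0.72), writing power rises to about 0.75 to 0.78. That is still short of 0.8, so the restatement in item 1 is needed either way.

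The cost is one rerun of existing code and a few sentences of text. No participants are added. The price is a less favourable power statement.

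### The within-subject benchmark and the repeated-measures argument do not establish power for the pupil co-primary outcome, which is analysed as a between-arm comparison of mean change

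*Protocol article*

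**What the plan says.** The protocol article's Sample size {14} section bases the number on one of the two primary outcomes: "We opt to base our sample size estimation on writing performance, but not on the other primary outcome, cognitive effort, for two reasons". The first reason is that no earlier effect size was found for generative AI on physiologically measured effort. The second is a hedged expectation that "our physiological measure of cognitive effort may likely be powered once the sample size satisfies our behavioral measure of writing performance". Two supports are given for that expectation. One is that N-back pupillometry studies usually enrol 20–50 people in within-subject trials, offered as a rough guide to the number needed. The other is that pupil size is recorded as a time series, and "Repeated outcome measures generally can enhance statistical power by taking into account within-subject variability". The section concedes that this trial is between-subject, but sets the repeated-measures argument against that concession.

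Statistical methods for primary and secondary outcomes {20a} specifies "cognitive effort as measured by mean changes in pupil size, will also be treated as a continuous variable", analysed by OLS with heteroskedasticity-robust standard errors. It names no participant random effect, clustering or within-person term for this outcome. Participant random effects appear only for the secondary fNIRS outcome. The same section says that "the adjusted significance threshold is set at *α* = 0.05/2 = 0.025", and that poor-quality pupil recordings will be excluded. It gives no expected rate.

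**The concern.** Each participant writes under one condition only, so treatment does not vary within a person. A within-subject study cancels stable differences between people; a parallel-group comparison of participant means does not. The two supports describe designs or gains that the planned contrast does not have, or has only in part.

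Cognitive effort is one of two primary outcomes and is central to the research question. A reader who accepts the sample size reasoning could take a non-significant pupil result as evidence that ChatGPT leaves cognitive effort unchanged, when the trial may simply not have been able to detect a moderate effect.

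**Working it through.** **1. Inputs.** From Sample size {14}: "an anticipated effect size of Cohen’s *d* = 0.45", "equal and standardized standard deviations between the two conditions", and "a minimum of 160 participants would be necessary to achieve a statistical power greater than 0.8 under an alpha level of 0.05". From Trial design {8}: 1:1 allocation, so 80 per arm. From {20a}: alpha 0.025 for each primary outcome. Two-sided testing is assumed, because sidedness is not stated. The documents give no pupil effect size, SD, within-person correlation or exclusion rate.

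**2. The plan's own figure.** With SD = 1, n per arm = 2(z₀.₉₇₅ + z₀.₈)²/d² = 2(1.960 + 0.842)²/0.45² = 77.5, rounded up to 78, or 156 in total. The t-test solution is 157 in total. Power at 80 per arm is 0.808 by t-test. The stated 160 is reproduced, but for writing performance at alpha 0.05.

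**3. What 160 can detect on the pupil outcome.** Take one mean per participant, a two-sided two-sample t-test and 80% power. The normal approximation at alpha 0.025 is d = (2.241 + 0.842)·√(2/80) = 0.487. The t-test values are:

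| Usable per arm | Alpha | Detectable d |
|---|---|---|
| 80 | 0.05 | 0.446 |
| 80 | 0.025 | 0.491 |
| 72 (10% excluded, assumed) | 0.025 | 0.518 |
| 64 (20% excluded, assumed) | 0.025 | 0.551 |

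The step from 0.446 to 0.491 comes wholly from the Bonferroni threshold. The later steps come from the assumed exclusions. With 80 per arm at alpha 0.025, power is 0.36 at d = 0.3, 0.61 at d = 0.4, 0.72 at d = 0.45 and 0.815 at d = 0.5.

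**4. What repeated samples add.** If k readings per person have intraclass correlation ICC (treated as exchangeable), the variance of a person's mean is SD²·[ICC + (1 − ICC)/k]. At an assumed ICC of 0.5 the bracket is 0.55 for k = 10 and 0.505 for k = 100, with a floor of 0.5. At an assumed ICC of 0.9 it is 0.91, 0.901 and 0.9. Relative to a single reading, d can grow by at most 1/√ICC: 1.41 and 1.05 respectively. The floor is between-person variance, and more samples per person cannot lower it.

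A mixed model would not change this. In 20 simulated balanced datasets (80 per arm, 10 values per person, ICC 0.5), a random-intercept model gave the same treatment estimate as OLS on the means, with standard error ratios of 0.9999 to 1.0000.

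**5. What the 20–50 benchmark translates to.** A paired comparison of N people has variance 2σ²(1 − r)/N. A two-arm comparison with n per arm has 2σ²/n. Setting them equal gives n = N/(1 − r). The within-person correlation r is assumed throughout:

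| Assumed r | N = 20 | N = 50 |
|---|---|---|
| 0.5 | 40 per arm | 100 per arm |
| 0.8 | 100 per arm | 250 per arm |
| 0.9 | 200 per arm | 500 per arm |

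The planned 80 per arm lies inside the range at r = 0.5 and below it at r = 0.8 and 0.9. The conversion compares precision only. It does not show that an N-back effect resembles the effect of ChatGPT on mean pupil change during essay writing.

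**The case against.** Several points on the other side stand. The protocol's language is hedged, and it volunteers the design difference, so it would be wrong to say that it asserts adequate power. Correction to each person's own resting baseline removes part of the stable difference in pupil size, and averaging a long recording reduces noise, so repeated recording has real value. The secondary covariate-adjusted analyses may also gain some precision. The pupil argument did not set the sample size, and the trial describes its framework as exploratory.

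These points do not repair the argument. The hedge and the concession are followed directly by the repeated-measures reasoning, which is offered as the answer to the design difference. Baseline correction and averaging act on part of the variance; what remains between people still governs the comparison of arms.

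A reader might infer that the pupil outcome is underpowered. The documents do not support that: they give no pupil effect size, and power at alpha 0.025 is about 0.815 if the true between-person d is 0.5. A reader might also infer from the per-arm conversion that 160 is too few. That depends entirely on an assumed correlation, and at r = 0.5 the planned size falls within the converted range.

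**Conclusion.** The concern holds as a fault in the justification. Neither the 20–50 benchmark nor the repeated-measures argument establishes power for a between-arm contrast of mean pupil change. Power of 80% at the planned threshold requires a between-person difference of about 0.49 SD with all recordings usable, or about 0.52 to 0.55 SD with 10% to 20% excluded. The protocol neither states nor supports an effect of that size for this outcome.

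These figures assume one value per participant (the most natural reading of {20a}), two-sided tests, equal variances and no covariate adjustment; the exclusion rates are illustrative. The mismatch between alpha 0.05 for sizing and 0.025 for analysis accounts for the step from about 0.45 to 0.49. It is a related but separate issue and should not add weight here.

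**What to change.** In Sample size {14}:

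- Replace the within-subject N-back benchmark with the detectable standardized difference for the planned analysis at 80% power and alpha 0.025: about 0.49 with 80 usable recordings per arm, and about 0.52 or 0.55 under 10% or 20% exclusion, with the rates labelled as assumptions.
- Keep the repeated-measures sentence only in qualified form: averaging and baseline correction reduce noise in each participant's value but do not remove the remaining between-person variance.
- If the benchmark is still converted to a per-arm size, label the conversion as resting on an assumed within-person correlation.
- State that a non-significant pupil result does not rule out effects smaller than the detectable difference.

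The cost is text only, with no change to sample size, outcome or analysis. The power statement for this outcome becomes less favourable.
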